## Abstract

**Background:**

Knee osteoarthritis (KOA) is a prevalent condition causing significant pain and functional impairment. Acupuncture has shown promise as an adjunctive therapy, but conventional manual selection of acupoints lacks standardization. The Acugraph system provides a computerized method for identifying acupoints, potentially enhancing treatment precision.

**Objective:**

This study aims to compare the effects of computerized Acugraph-guided acupuncture versus manually selected acupuncture as adjuncts to physiotherapy in managing KOA.

**Methods:**

A randomized, double-blind controlled trial will be conducted with 50 participants diagnosed with mild to moderate KOA. Participants will be randomly assigned to one of two groups: Group 1 Comp-AcuPhysio (n = 25), receiving Acugraph-guided acupuncture with physiotherapy, or Group 2 Man-AcuPhysio (n = 25), receiving manually selected acupuncture with physiotherapy. Both groups will undergo 12 weekly treatment sessions, each lasting 60 minutes. Outcome measures, including the Knee Injury and Osteoarthritis Outcome Score, active knee flexion range, Timed Up and Go test, Visual Analog Scale for pain, Short Form-36 health survey, and Personal Integrated Energetics score, will be assessed at baseline and immediately post-intervention. An intention-to-treat analysis will be applied. Changes from baseline to 12 weeks will be analyzed using repeated measures analysis of variance for both within-group and between-group comparisons.

**Results:**

This study will provide a definitive assessment of the effectiveness of computerized Acugraph-guided acupuncture compared to manually selected acupuncture as supplementary treatments alongside KOA physiotherapeutic rehabilitation.

**Conclusion:**

This trial will offer insights into how incorporating technology-driven approaches, such as Acugraph, with physiotherapy can enhance the customization and effectiveness of KOA management, leading to improved clinical outcomes. These results could advocate for the integration of technological tools in acupuncture to boost treatment precision and efficacy for KOA.

**Trial registration:**

Australian New Zealand Clinical Trials Registry (ACTRN12624000646549p).

## Introduction

Knee osteoarthritis (KOA) is a multifaceted condition affecting various components of the knee joint, including calcified cartilage, subchondral bone, ligaments, and synovial fluid [1]. The persistent inflammatory response associated with KOA exacerbates impairments and imposes significant functional limitations [1, 2]. Individuals suffering from KOA commonly experience symptoms such as knee pain, restricted movement, joint stiffness, muscle weakness, impaired mobility, and balance issues [2]. Projections indicate that the number of affected individuals worldwide will increase to 130 million by 2050, placing a substantial burden on healthcare systems globally [3]. Healthcare providers often resort to nonsteroidal anti-inflammatory drugs and intra-articular injections to alleviate pain and delay surgical intervention [4]. However, prolonged pharmacological therapy frequently leads to adverse effects such as peptic ulcers and gastrointestinal bleeding, underscoring the need for alternative, non-pharmacological interventions [4]. Recognizing the limitations of pharmacotherapy, non-pharmacological modalities like physiotherapeutic rehabilitation have gained traction as viable alternatives in KOA management, as endorsed by international guidelines and supported by empirical evidence [5–8]. However, challenges persist in achieving optimal outcomes, with factors such as patient adherence to exercise regimens and the persistence of pain acting as barriers to effective treatment [9, 10].

In this context, acupuncture, with a history spanning over three millennia and originating from China, has garnered attention for its potential in managing chronic musculoskeletal pain [11, 12]. Recent studies have contributed to the growing body of evidence supporting acupuncture’s efficacy in alleviating pain, especially in musculoskeletal disorders [13–15]. Theoretically, acupuncture is believed to elicit the release of endorphins, modulate the nervous system, and induce relaxation, thereby reducing pain signals [16]. Crucially, the effectiveness of acupuncture hinges on the precise selection of acupoints tailored to the individual patient’s physiological condition, highlighting the importance of personalized treatment approaches [16, 17]. While acupuncture holds promise as a safe adjunctive therapy for KOA management, its integration with physiotherapeutic exercise warrants further investigation [11, 14]. The lack of high-quality clinical evidence and standardization in acupuncture techniques and acupoint selection hinder its widespread adoption [6, 11, 14]. Conventionally, acupoint selection has been based on manual methods guided by practitioner expertise, which is highly subjective and reliant on the acupuncturist’s experience and preference [18, 19]. This approach lacks standardization and may introduce variability in treatment outcomes, posing challenges to reproducibility and comparability across studies [18–20].

Moreover, the absence of clear guidelines on acupuncture modalities and acupoint selection further complicates its application in clinical settings [17, 20]. Clinical trials utilizing fixed acupoint protocols have been criticized for disregarding the individualized treatment approaches inherent in traditional Chinese medicine practice [21]. Additionally, only 40% of guidelines issued by conventional medical organizations detail the types of acupuncture, such as manual, electro-acupuncture, or acupressure, and only 5% of these guidelines specify the range of acupuncture points selected [17]. To address this limitation, modern acupuncture has embraced technological innovations such as Acugraph analysis. Acugraph is a device that measures electrical impedance at various points on the body, creating graphical representations that help acupuncturists visualize and analyze the balance and vitality of meridians. This objective assessment of acupoints guides treatment selection [20, 22]. By incorporating technology into acupuncture practice, Acugraph offers a standardized and reproducible approach to acupoint selection, enhancing treatment reliability and consistency [22, 23]. However, more investigation is needed to substantiate the effectiveness of computerized methods of identifying acupoints, particularly in the management of KOA.

In light of these considerations, this study seeks to address the gaps in the existing literature by comparing the effects of computerized point-specific acupuncture, determined by Acugraph, with manual preference acupuncture as adjuncts to physiotherapeutic exercise in KOA management. By rigorously evaluating the synergistic effects of acupuncture and physiotherapy, this research aims to provide valuable insights into optimizing non-pharmacological interventions for KOA.

## Materials and methods

### Study design

This study will utilize a parallel-group (two arms), double-blinded, randomized controlled trial design. The study protocol follows the CONSORT guidelines for clinical trials and meets the recommended criteria outlined in the SPIRIT checklist (S1 File. SPIRIT Checklist). Fig 1 illustrates the details of the schedule for enrollment, interventions, and assessments at each time point.

**Fig 1 pone.0313761.g001:**
[figure not shown]
Schedule of enrolment, interventions, and assessments.

### Ethical approval and trial registration

Ethical approval was obtained from the Secretariat of the Research Ethics Committee at Universiti Kebangsaan Malaysia (ID: UKM PPI/111/8/JEP-2024-244), approved on 14^th^ June 2024, ensuring compliance with the ethical principles outlined in the Helsinki Declaration (S2 File. Ethical approval letter). The trial protocol has been registered with the Australian New Zealand Clinical Trials Registry (ANZCTR), which is approved under the World Health Organization International Clinical Trials Registry Platform (WHO ICTRP), and the registration number is ACTRN12624000646549p. Any relevant study protocol modifications, along with their justification, will be communicated to and updated with the ethics committee and trial registry.

### Study setting

The study will be conducted at Grand Care Rehab Seremban (Physiotherapy & Acupuncture), Malaysia. Grand Care Rehab Seremban is an established clinical setup that offers conventional physiotherapy rehabilitation services and specializes in complementary medicine approaches, particularly traditional Chinese medicine acupuncture. Recruitment strategies include: (i) utilizing social media and online forums, (ii) collaborating with local organizations and community groups, (iii) implementing referral programs, and (iv) distributing brochures and posters in targeted areas.

### Target population

The inclusion criteria are as follows: (i) adults aged 18 years and above of both genders, (ii) diagnosed with unilateral or bilateral KOA by an orthopedic physician, with radiologic confirmation of KOA grade 2 (mild) or 3 (moderate) according to the Kellgren-Lawrence classification based on an X-ray performed within the last 12 months, and (iii) capable of participating in the intervention and assessment program without restrictions. In cases of bilateral KOA involvement, the more painful knee will be selected for outcome evaluation. The exclusion criteria include: (i) those with recent knee trauma, ligament damage, fracture, or surgery within the past 6 months, (ii) a history of local knee tumor or malignancy, recent prolotherapy, hyaluronic acid, or corticosteroid injections within the past 6 months, and (iii) individuals who oversensitive to needles.

### Sample size calculation

The sample size was calculated using G*Power software version 3.1.9.7, with a focus on achieving a robust estimate for detecting clinically meaningful changes. Specifically, a minimum clinically important difference (MCID) of 11.1 points, with a standard deviation (SD) of 3.8 points, was used based on established values for the primary outcome, the total Knee Injury and Osteoarthritis Outcome Score (KOOS) [24]. This estimation considered a power of 80%, an effect size of 0.2, a significance level of 5%, and an anticipated dropout rate of 20% [25, 26]. Consequently, the total calculated sample size was 50 participants, evenly divided into two groups of 25 participants each. KOOS was selected as the primary outcome measure for this study due to its comprehensive assessment of key domains relevant to KOA, including pain, symptoms, activities of daily living, sport and recreation, and quality of life [27]. The tool has been widely validated in populations with KOA and is sensitive to changes following interventions, making it an appropriate and robust measure for capturing patient-reported outcomes in this context [27].

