Additionally, a per-protocol analysis will be conducted to compare findings from participants who adhered strictly to the protocol [47]. This comparison will help assess any differences in outcomes between the two approaches [47]. To examine differences between the both groups over time, a repeated measures ANOVA will be employed to assess changes in KOOS, AKF, TUG, VAS, SF-36, and PIE scores over time (time main effect) and to evaluate whether these changes over time differed between the two groups (group-by-time interaction). Additionally, to assess the extent of variation between groups, the effect size of each variable will be calculated using Cohen’s d, where values of 0.2, 0.5, and 0.8 indicate small, medium, and large effects, respectively [26]. In addition, subgroup analysis will be performed based on key factors such as age groups, BMI, and disease severity (mild vs. moderate), as these variables are considered important contributors to outcomes in KOA. The analysis will help identify whether the intervention effects vary across these subgroups.

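### The sample-size inputs contradict each other (11.1/3.8 is a standardised difference of 2.92, yet 0.2 is stated), and 50 participants do not give 80% power for an effect size of 0.2 read as Cohen's d

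*Protocol article*

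**What the plan says.** The Sample size calculation section says G*Power was used with "a minimum clinically important difference (MCID) of 11.1 points, with a standard deviation (SD) of 3.8 points", taken as established values for total KOOS, the primary outcome. The next sentence says the estimate considered "a power of 80%, an effect size of 0.2, a significance level of 5%, and an anticipated dropout rate of 20" per cent. The result is 50 participants, 25 per group. The section does not give the test, the sidedness, the effect-size metric or a correlation between repeated measurements.

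The only effect-size metric defined in the article is Cohen's d, in the Data analysis section, "where values of 0.2, 0.5, and 0.8 indicate small, medium, and large effects" respectively. That sentence cites one of the two references attached to the sample-size inputs. The planned comparison is the group-by-time interaction of a repeated measures ANOVA with two time points, baseline and immediately post-intervention.

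The Results paragraph of the abstract says: "This study will provide a definitive assessment of the effectiveness of computerized Acugraph-guided acupuncture" compared with manual selection.

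**The concern.** One calculation has been given two effect sizes. A difference and its SD already fix the standardised difference, so a separate value of 0.2 is either redundant or contradictory, and here it is contradictory.

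If 0.2 is a small Cohen's d, a total of 50 is far too few. If 11.1 with SD 3.8 is right, 50 is several times too many. In either case the article's only justification for the trial's size cannot be reproduced from its own numbers.

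This matters because both arms receive needle acupuncture and the same physiotherapy. The contrast is only how the points are chosen. If the trial is presented as definitive and as powered for a small effect, a non-significant result could be taken to show that the two methods work equally well, which a trial of this size could not support.

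**Working it through.** **Inputs from the article.** Difference 11.1 points; SD 3.8; stated effect size 0.2; power 80%; significance 5%; dropout 20%; 1:1 allocation; N = 50. Assumed here: a two-sided test. Evaluable number: 50 × (1 − 0.20) = 40, or 20 per group.

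**Step 1: do the inputs agree?** d = 11.1/3.8 = 2.92, and 2.92/0.2 = 14.6. For 11.1 points to equal d = 0.2, the SD would have to be 11.1/0.2 = 55.5. On a 0–100 score an SD cannot exceed 50, so no feasible SD reconciles the two.

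**Step 2: try to reproduce 50 with a two-sample t-test.** Power comes from the noncentral t distribution with 2n − 2 degrees of freedom and noncentrality d√(n/2), where n is the number per group.

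| Effect size | n per group for 80% | Total | Total after 20% dropout |
|---|---|---|---|
| d = 0.2 | 394 | 788 | 788/0.8 = 985 |
| d = 2.92 | 4 (power 93%; 76% with 3) | 8 | 8/0.8 = 10 |

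Neither is 50. One-sided testing does not help: 310 per group (775 in total after dropout) for d = 0.2, and 3 per group for d = 2.92.

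**Step 3: power at the planned size for d = 0.2.** It is 10.7% with 25 per group and 9.5% with 20 per group.

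**Step 4: try other tests with 0.2 read as Cohen's f.**
- One-way ANOVA: 200 in total before dropout; 28% power at N = 50.
- Repeated-measures between-group effect: 102 to 180 in total for correlations of 0 to 0.8.
- Repeated-measures group-by-time interaction with two times, noncentrality f² × N × 2/(1 − ρ), with the correlation ρ assumed:

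| ρ (assumed) | N before dropout | N/(1 − 0.2) | Power, 50 analysed | Power, 40 analysed |
|---|---|---|---|---|
| 0 | 102 | 128 | 50% | 41% |
| 0.5 | 52 | 65 | 79.1% | 69.3% |
| 0.6 | 42 | 53 | 87.3% | 78.7% |
| 0.8 | 22 | 28 | 99.2% | 97.4% |

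Forty evaluable, hence 50 enrolled, is reached at ρ of about 0.62.

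**Step 5: what f = 0.2 means in that design.** The difference between groups in change is 4 × f × SD = 4 × 0.2 × SD = 0.8 SD. With SD 3.8 that is 3.0 points, not 11.1. At ρ = 0.62 the SD of change is √(2 × (1 − 0.62)) = 0.87 SD, so the difference is 0.8/0.87 = 0.92 SD of change.

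**Step 6: what n = 50 can detect (t-test, 80% power).** The detectable d is 0.91 with 20 per group and 0.81 with 25 per group. The 11.1-point difference has 80% power with 20 per group only if the SD is at most 11.1/0.909 = 12.2. The SDs below are assumptions; the article gives none except 3.8.

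| Assumed SD | Detectable difference (0.909 × SD) | Power for 11.1 points, 20 per group |
|---|---|---|
| 10 | 9.1 | 93% |
| 15 | 13.6 | 63% |
| 20 | 18.2 | 40% |

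**Step 7: a query on the SD.** If scores were roughly normal, an SD of 3.8 would put 95% of participants within 1.96 × 3.8 = 7.4 points of the mean. That looks narrow for a between-person SD on a 0–100 score in a sample mixing grades 2 and 3. The cited source is not available here, so the origin of the figure cannot be checked.

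**The case against.** The best defence is that 0.2 was never meant as Cohen's d. The sample-size section names no metric, and the Data analysis section introduces d for reporting results. The planned test is a repeated-measures interaction, for which Cohen's f is a natural input. With f = 0.2 and a correlation of 0.5, power is 79.1% if all 50 are analysed. At a correlation of 0.6, N is 42, and multiplying by 1.2 instead of dividing by 0.8 gives about 50 or 51. This could well be how the figure arose.

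Part of this stands. The power figures near 10% depend on reading 0.2 as d, and a route to about 50 exists. But that route needs a metric and a correlation that the article does not state. The first version ignores the stated dropout, and the second leaves 78.7% power with 40 analysed. Neither reconciles 0.2 with 11.1/3.8. The f reading also leads to the same sensitivity: about 0.92 SD of change, against 0.91 from the t-test.

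Three further objections are fair:
- An article may leave the G*Power settings to the full protocol, so the unnamed test is not a fault in itself. The fault is that the inputs which are given conflict.
- The article does not say that a null result would be read as equivalence. That is a risk, not a stated intention.
- The detectable difference is large on the article's own scale; calling it more than that would overstate the case.

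**Conclusion.** The paragraph is wrong as written and must be corrected. The conflict between 11.1 with SD 3.8 (d = 2.92) and an effect size of 0.2 holds under every reading, and neither value gives 50 from the stated inputs.

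The stated 80% power fails under the only metric the article defines: for d = 0.2 it is 9.5% with 20 evaluable per group and 10.7% with 25 (two-sided 5%). If 0.2 is an unstated Cohen's f for the interaction, power with 40 analysed runs from 41% to 97% for correlations of 0 to 0.8, so 80% cannot be confirmed.

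Under both readings that approach n = 50, the trial has 80% power only for a difference of about 0.9 SD of the analysed quantity. Whether this covers 11.1 KOOS points depends on an SD that the article does not credibly supply; the limit is 12.2. The claim of a definitive assessment is not supported.

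**What to change.** Keep n = 50 and restate its basis in the Sample size calculation section:
- Delete the effect size of 0.2 and the SD of 3.8, and name the test. If the original G*Power run can be recovered, also report its metric, correlation and dropout formula.
- State that 20 evaluable participants per group give 80% power, at two-sided 5%, for a standardised between-group difference of 0.91, and that this equals 11.1 KOOS points only if the SD of the analysed quantity is 12.2 or less.
- Give the detectable differences for SDs of 10, 15 and 20 (9.1, 13.6 and 18.2 points), labelled as assumptions.
- In the abstract's Results paragraph, replace the word definitive with wording that fits this precision.

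The cost is one rewritten paragraph, one abstract sentence, and an update to the registry and the ethics committee. No extra participants are needed, and neither the design nor the analysis changes. The stated sensitivity becomes less favourable than the present text suggests.

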### Screening, recruitment, and randomization

Eligible participants will be screened by a research assistant who is not involved in the intervention or outcome assessment. Those who meet the criteria will be provided with verbal and written information, followed by obtaining signed informed consent. Sociodemographic details will be collected, and each participant will be assigned a unique identification number to safeguard privacy and confidentiality. Participants (n = 50) will be randomly allocated to one of two groups at a 1:1 ratio: (i) Group 1 Comp-AcuPhysio (n = 25) which uses a computerized method of acupoint selection as an adjunct to physiotherapy, or (ii) Group 2 Man-AcuPhysio (n = 25) which uses a manual method of acupoint selection as an adjunct to physiotherapy. The randomization will be performed using a computerized simple block randomization method. The randomization process will be conducted by the principal investigator, who is not involved in the intervention or outcome assessment. Allocation concealment will be maintained through sealed opaque envelopes describing the treatment group. Fig 2 illustrates the study flowchart.

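### Allocation is not stratified by Kellgren-Lawrence grade, although grade is known at entry and the protocol treats it as prognostic; this is valid, and two blocked lists plus grade terms in the model would be a cheap improvement.

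*Protocol article*

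**What the plan says.** Under Screening, recruitment, and randomization the protocol article says: "Participants (n = 50) will be randomly allocated to one of two groups at a 1:1 ratio", and then "The randomization will be performed using a computerized simple block randomization method". Neither that section nor any other mentions stratification or minimisation.

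Under Target population, entry requires "radiologic confirmation of KOA grade 2 (mild) or 3 (moderate) according to the Kellgren-Lawrence classification", read from an X-ray no more than 12 months old. When both knees are affected, the more painful one is evaluated.

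Under Data analysis, subgroup analyses are planned by age group, BMI and "disease severity (mild vs. moderate), as these variables are considered important contributors to outcomes in KOA". The same section describes the main comparison as a repeated measures ANOVA and names two terms: the time effect and the group-by-time interaction.

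**The concern.** Blocking equalises the number of participants per arm. It does nothing to equalise the mix of mild and moderate disease. Here a two-level factor that the protocol itself regards as relevant to outcome is in hand for every participant before the envelope is opened, and the allocation does not use it. Stratification is part of the allocation design, so an analysis plan written later cannot supply it.

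At 25 per arm, chance differences in grade are not rare. With two time points, the group-by-time test is a comparison of mean change between arms. It removes a constant effect of grade on the level of the Knee Injury and Osteoarthritis Outcome Score (KOOS), but not an effect of grade on change. If moderate knees improve by a different amount, an uneven split moves the estimated arm difference for reasons unrelated to how acupoints were chosen. Both arms receive acupuncture and the same physiotherapy, so the true contrast may be small, and a visible imbalance in severity would make a small observed difference harder to defend.

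**Working it through.** The plan gives no figure for imbalance, so there is none to reproduce. The arm size of 25 is taken as stated; how it was derived is a separate matter and does not affect this point.

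**Inputs**
- From the document: 50 participants, 1:1, 25 per arm, no stratification; minimum clinically important difference (MCID) 11.1 KOOS points and SD 3.8 (Sample size calculation).
- Assumed, because the document is silent: share with grade 3 of 30% to 70%; block size 4; effect of grade on the analysed change of 0.5 SD.

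**1. Chance of a 20-point imbalance.** Let K of the 50 have grade 3, and let X of these fall in one arm. With equal arms, X is hypergeometric (50, K, 25) and the difference in counts is 2X − K. A gap of 20 percentage points is 0.20 × 25 = 5 participants.
- K fixed: P(|2X − K| ≥ 5) = 0.258 at K = 25; 0.156 at K = 24 or 26; 0.148 at K = 20 or 30; 0.217 at K = 15 or 35.
- These values jump because 2X − K is odd or even according to K. For even K, a gap of at least 5 is really a gap of at least 6. K is not known at planning, so no single value of K should be quoted.
- K random, Binomial(50, p), averaging over K: 16% at p = 0.3 or 0.7; 19% at p = 0.4 or 0.6; 20% at p = 0.5.
- Cross-check by simulating unstratified blocks of 4 (20,000 runs): about 15% at p = 0.3 and 19% at p = 0.5.

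**2. Effect on the arm difference.** Shift = imbalance × grade effect = 0.20 × 0.5 SD = 0.10 SD. Standard error of the arm difference = √(2/25) = 0.28 SD. Ratio = 0.10/0.28 = 0.35, about one third of a standard error.

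In points, on the plan's SD: 0.10 × 3.8 = 0.38, and 0.38/11.1 = 3% of the MCID. If the two grades instead differed by an assumed 5 to 15 points in change, the shift would be 0.20 × 5 = 1 to 0.20 × 15 = 3 points, or 9% to 27% of 11.1. That assumption is far stronger: 5/3.8 = 1.3 to 15/3.8 = 3.9 of the plan's SDs.

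**3. What the change buys.**
- Balance: with blocks of 4 within each grade, the arms differ by at most 2 participants per grade. In simulation the largest gap in the grade 3 share was about 7 percentage points, and none reached 10.
- Precision: with half the participants at grade 3, a 0.5 SD effect adds 0.5² × 0.5 × 0.5 = 0.0625 to a within-grade variance of 1. The standard error without grade in the model is √1.0625 × 0.283 = 0.29 SD; with grade it is 0.28 SD. Simulation puts the gain in power at only about one to two percentage points, and stratifying while leaving grade out of the model adds no power.

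**4. Arm sizes after the change.** Since 50 = 12 × 4 + 2, the two strata leave incomplete blocks of 0 and 2, 1 and 1, or 3 and 3 participants. Each case gives a total difference of at most 2, so 24/26 at worst. A single list in blocks of 4 can also end 24/26.

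**The case against.** The strongest reply is that unstratified permuted blocks at a single centre are a standard, sound method, and that choosing grade as a stratification factor is a preference. Much of this stands. Randomisation without stratification leaves the test unbiased and the type I error intact, and the confidence interval already allows for chance imbalance. The protocol mentions severity to justify subgroup analyses and nowhere promises balance, so the two sections do not contradict each other. Age and BMI are named on the same footing as severity; grade is singled out here because it is already binary and fixed at entry. The document gives no size for an effect of grade on change in KOOS.

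Four stronger readings might tempt a reader, and the document supports none of them.
- That the chance of a 20-point imbalance is 26%. This holds only if exactly 25 participants have grade 3; one more or one fewer gives 16%.
- That the main analysis is known to ignore severity. The article names two terms but does not exclude covariates, and a condensed article may leave these to an analysis plan that is not shown.
- That the 0.1 SD shift is half the targeted effect. The sample size section lists an effect size of 0.2 without naming its metric, so the comparison cannot be made safely.
- That unequal arms within a grade would invalidate the severity subgroups. They would cost a little efficiency and no more.

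What remains is that a cheap safeguard, based on information already collected, is left unused.

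**Conclusion.** The point holds as a modest design improvement and not as an error of validity. Under the stated allocation there is roughly a one-in-six to one-in-five chance that the arms differ by 20 percentage points or more in grade 3, over assumed shares of 30% to 70%. With an assumed 0.5 SD effect of grade on change, that moves the arm difference by about 0.1 SD, one third of its standard error. A smaller effect of grade makes the matter smaller in proportion, and a purely constant effect on KOOS level removes it from the group-by-time test altogether. The expected gain in precision is slight and comes from having grade in the model. Stratifying chiefly ensures that a small observed difference cannot be put down to an uneven mix of severity.

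**What to change.** Prepare two blocked randomisation lists, one for Kellgren-Lawrence grade 2 and one for grade 3 of the knee to be evaluated, with the opaque envelopes numbered within each list. State in the plan that the primary repeated measures model includes grade and its interaction with time. The interaction is needed because the grade main effect alone does not adjust the comparison of change. Leave age and BMI out of the stratification, as further strata would be too thin at 50 participants.

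The article expected recruitment from July 2024, so allocation may have begun. In that case leave the allocation alone and add the two grade terms to the model before unblinding. This recovers part of the precision gain, though not the assurance of balance.

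The cost is one more list and set of envelopes to manage, a possible 24/26 split, and one or two model degrees of freedom. No new data are needed.
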